### Data collection

At the time of enrollment, information about the history of PCOS diagnosis, menstrual cycle demographic characteristics, socioeconomic status, alcohol consumption, smoking habit, self-reported morbidity, obstetric history, first-degree family history of hypertension, diabetes, stroke, hyperlipidemia, and obesity will be obtained using a baseline questionnaire. Clinical information on the maternal and neonatal outcomes mentioned above will be collected from outpatient and inpatient electronic records in four centers and will be confirmed by the investigators.

### Statistical methods

#### Sample size calculation

A recent meta-analysis reported an estimated clinical pregnancy rate of 26% in PCOS patients undergoing IVF [24]. Our team has revealed that approximately 30% of PCOS patients have *Lactobacillus* deficiency (PCOS-LD), which presents as lower levels of *Lactobacillus* (< 50%) in the vagina [7]. Our unpublished data suggested a clinical pregnancy rate of 17.65% in patients with PCOS-LD, while a clinical pregnancy rate of 41.82% was reported in PCOS patients without *Lactobacillus* deficiency (PCOS-non-LD). Moreover, our team previously reported a clinical pregnancy rate of 49.69% in patients who underwent IVF due to tubal blockage [25]. To improve the clinical pregnancy rate among infertile PCOS-LD patients to the level of that among PCOS-non-LD patients, or even to the clinical pregnancy rate among patients with tubal blockage, we hypothesized a 20% increase in the clinical pregnancy rate in our RCT. Assuming a clinically important 20% increase in the rate of clinical pregnancy in the intervention arm and allowing for a 15% dropout rate, the calculated sample size of 260 subjects (130 per group) will provide 95% power with a one-tailed alpha error of 0.025. Thus, we aim to recruit 300 women in total (150 per group).

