**Methods/design:**

This is a protocol for a multicenter, open-label, randomized controlled trial in China. Women diagnosed with PCOS who are undergoing IVF-FET treatment will be recruited. Allocation to the intervention/control arms at a ratio of 1:1 will be executed by an electronic randomization system. Participants in the intervention arm will receive the live *Lactobacillus* capsule vaginally for 10 consecutive days before embryo transfer, while those in the control arm will receive standard individualized care. The primary outcomes will be the clinical pregnancy rate, implantation rate, and live birth rate. 16S rRNA sequencing and liquid chromatography–mass spectrometry will be conducted to evaluate the LGT microbiome and systemic metabonomics before and after the intervention. A sample of 260 participants will provide 95% power to detect a 20% increase in the rate of clinical pregnancy (*α* = 0.025, one-tailed test, 15% dropout rate). A total of 300 participants will be recruited.

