### Participants

#### Inclusion criteria

A total of 20- to 35-year-old women who have been diagnosed with PCOS according to the Rotterdam Criteria and plan to undergo IVF–FET will be recruited. Quick screening of the abundance of *Lactobacillus* spp. will be performed by real-time quantitative polymerase chain reaction (RT–qPCR), which will be specified later. Women with PCOS with *Lactobacillus* spp. accounting for less than 80% of the vaginal microbiome who volunteer to participate will be eligible for this study.

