#### Statistical analysis

Categorical variables will be presented as counts with percentages, e.g., *n* (%). Normally distributed data will be shown as the means with standard deviations, e.g., means ± SDs, while nonnormally distributed data will be expressed as medians with interquartile ranges, e.g., medians (IQRs). Student’s *t* test for continuous variables with normal distributions and the nonparametric

Kruskal–Wallis test for nonnormally distributed data will be applied for comparisons of significant differences between the 2 groups. The Pearson chi-square test will be used for categorical data. For binary observational endpoints, risk ratios with 95% confidence intervals will be calculated by binomial regression with and without adjustment for potentially confounding baseline values. In this study, the main analyses will be conducted using an intention-to-treat (ITT) model, in which all participants will be included based on random assignment regardless of study completion. For outcomes collected at different time points, a repeated measurements design using a generalized estimating equation (GEE) model will be used to fit outcomes that are measured at each time point so that all the participants might be included in the analyses, even if there are missing data for some of the follow-up points. A multiple imputation model will be used to process the missing data. Additionally, statistical analyses of the baseline characteristics of participants who remain in the study and those who are lost to follow-up will also be performed to explore whether there is differential dropout. All statistical analyses will be conducted using the SPSS software (version 25.0) and R software (version 4.0.2). A two-sided *p* value < 0.05 will be considered significant.

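### The stated 95% power rests on a pregnancy rate from women with under 50% Lactobacillus, but the trial enrols women up to 80%, so the figure is unsupported for the randomised population; the 15% dropout allowance is also attached to the wrong number

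*Protocol article*

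**What the plan says.** The Sample size calculation section of the protocol article cites several clinical pregnancy rates: 26% in PCOS patients undergoing IVF (a meta-analysis), 41.82% in PCOS patients without Lactobacillus deficiency, and 49.69% in patients with tubal blockage. For the deficient group it says: "Our unpublished data suggested a clinical pregnancy rate of 17.65% in patients with PCOS-LD". The same section defines deficiency (PCOS-LD) as Lactobacillus below 50% in the vagina. The stated aim is to bring PCOS-LD patients up to the rate of the non-deficient, or even to that of the tubal group.

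The effect is worded as follows: "Assuming a clinically important 20% increase in the rate of clinical pregnancy in the intervention arm". The section does not say to which control rate this is added. The error rate is one-sided 0.025 ("will provide 95% power with a one-tailed alpha error of 0.025"). This has the same critical value as the two-sided 0.05 in the Statistical analysis section, so there is no conflict there. The dropout allowance is tied to the 260: "allowing for a 15% dropout rate, the calculated sample size of 260 subjects (130 per group) will provide 95% power". The next sentence sets recruitment at 300, or 150 per group. The Abstract repeats it: "A sample of 260 participants will provide 95% power to detect a 20% increase in the rate of clinical pregnancy", with the 15% dropout in the bracket that follows and 300 recruited.

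The Inclusion criteria set a different threshold from the one behind 17.65%. Women with Lactobacillus "accounting for less than 80% of the vaginal microbiome who volunteer to participate will be eligible for this study".

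**The concern.** The power statement and the eligibility rule describe different groups. The planning rate appears to come from women below 50% Lactobacillus. The trial also takes women between 50% and 80%, whom the protocol's own definition would class as not deficient. The non-deficient group as a whole has a rate of 41.82%. Adding women from it would be expected to raise the control rate, and it may shrink the average effect because these women have less deficit to correct. The article gives no pregnancy rate for the under-80% population or for the 50–80% band, and does not explain the change of threshold.

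At stake is how a null result is read. It would be reported as coming from a trial with 95% power, when a higher control rate or a diluted effect could be part of the explanation.

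Two wording faults make the claim hard to audit. The dropout allowance is attached to 260, and the 20% increase is not said to be absolute.

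**Working it through.** **Inputs.** From Sample size calculation: one-sided alpha 0.025 (z = 1.960), power 95% (z = 1.645), a gain of 20, dropout 15%, 260 calculated, 300 recruited. Allocation is 1:1 (Recruitment and randomization). Control rates tried are those cited for PCOS: 17.65%, 26% and 41.82%.

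**Formulas** (two proportions, normal approximation, pooled variance under the null; d = p2 − p1, p̄ = (p1 + p2)/2):

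- n per arm = [1.960·√(2p̄(1−p̄)) + 1.645·√(p1(1−p1) + p2(1−p2))]² / d²
- power = Φ{[d·√n − 1.960·√(2p̄(1−p̄))] / √(p1(1−p1) + p2(1−p2))}

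**1. Reproducing the plan's figure.** For 17.65% against 37.65%, p̄ = 0.2765 and the two square roots are 0.6325 and 0.6165. So n = (1.2397 + 1.0141)²/0.04 = 127 per arm, 254 in total. This is close to 260, and 130 per arm gives 95.4%. Other formulas give about 124 per arm (unpooled) and 137 (continuity-corrected).

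The other PCOS rates do not fit: 26% against 46% needs 147 per arm (294), and 41.82% against 61.82% needs 160 per arm (320). A relative 20% increase on 17.65% would need about 3,260 per arm, so the 20% must mean percentage points.

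**2. Dropout.**

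| Reading | Evaluable | Power, 17.65% vs 37.65% |
|---|---|---|
| 260 already contains 15% dropout | 260 × 0.85 = 221 (110.5 per arm) | 91.9% |
| 300 recruited, 15% lost | 300 × 0.85 = 255 (127.5 per arm) | 95.1% |

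In the other direction, 254/0.85 = 299. So 260 is an evaluable number, and 300 is the number inflated for dropout.

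**3. Same 20-point gain, other cited control rates, 255 evaluable.**

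- 26% vs 46%: [0.2·√127.5 − 1.960 × 0.6788]/0.6639 = 1.40, power 91.9%. For 95%: 294 evaluable, 294/0.85 = 346 recruited.
- 41.82% vs 61.82%: power 89.6%. For 95%: 320 evaluable, 320/0.85 = 377 recruited.

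**4. Illustration of dilution.** Let w be the share of enrolled women at 50–80%. The article does not give w. Assume these women have the 41.82% rate and no benefit, and that the rest gain 20 points. Then control = 17.65(1−w) + 41.82w and effect = 20(1−w) points.

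| w | Control | Treated | Power, 255 evaluable |
|---|---|---|---|
| 0.1 | 20.07% | 38.07% | 89% |
| 0.2 | 22.48% | 38.48% | 80% |
| 0.3 | 24.90% | 38.90% | 67% |

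If every woman gains 20 points whatever her stratum, power stays at about 94%, 93% and 92% for the same three shares. The larger losses therefore come from the assumption of no benefit, not from the higher control rate.

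**The case against.** The strongest reply is that the power loss is assumed and not shown. The planning rate is inferred. No rate or share is given for the 50–80% band. The 41.82% belongs to all women who are not deficient, including those at 80% or above whom the trial excludes. If pregnancy rates rise with Lactobacillus, as the trial's rationale supposes, the band would lie below 41.82%. Nothing in the article says that these women cannot benefit, and the mention of the tubal-blockage rate (49.69%) leaves room for gain above 41.82%. All of this stands, and it is why the table in step 4 is only an illustration.

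A second reply is that the main analysis is by intention to treat with multiple imputation, so 255 may be pessimistic. With all 300 outcomes known, 26% against 46% gives 95.4%. That is an upper bound, because imputation does not restore all the missing information. At 41.82% the same 300 still give only 93.8%.

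A reader might also infer that dropout leaves the trial short, because 260 less 15% gives 91.9%. The documents do not support that: recruitment is 300, which leaves 255. Nor is 300 too few on the ground that 260/0.85 = 306. The requirement on the plan's apparent rates is 254, and 254/0.85 = 299.

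Finally, covariate choice and stratum estimates are often left to an analysis plan, and none is shown. This is fair, so a separate estimate in women below 50% is offered only as an option.

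**Conclusion.** The concern holds in a limited form. On the most plausible reading, the 95% power applies to 17.65% against 37.65% in women below 50% Lactobacillus. For the under-80% population actually randomised it is unsupported. With 255 evaluable and an unchanged 20-point gain, the shortfall is modest: 91.9% at 26% and about 90% at 41.82%. It becomes serious only if women at 50–80% form a sizeable share and benefit less. Under the illustrative assumptions, power is about 89%, 80% and 67% at shares of 10%, 20% and 30%.

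It would go too far to conclude that the trial is shown to be underpowered, or that the power figure belongs to a wholly different population. The women below 50% are a subset of those enrolled, and the article has no data on the remainder.

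The dropout allowance is misplaced in both the Abstract and the Sample size calculation section. It costs no power, because the 300 recruited covers it.

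**What to change.** Keep 300 and the eligibility rule, and change the text as follows.

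1. In the Abstract and in Sample size calculation, name the control rate and place the dropout correctly: about 254–260 evaluable, 300 recruited to allow for 15% dropout, 95% power for 17.65% against 37.65% (20 percentage points, not a relative 20%) in women with Lactobacillus below 50%.
2. Add the power for the under-80% population over a stated range of control rates (for example 17.65% to 41.82%) and of shares at 50–80%, with and without benefit in that band. The screening qPCR results can supply the share.
3. Name baseline qPCR Lactobacillus abundance as a covariate in the adjusted primary risk ratio. The Statistical analysis section already plans adjustment for baseline values without naming them, and every participant has this measurement from screening.

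Optionally, pre-specify an estimate in women below 50% as a supportive analysis.

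The cost is wording, a short sensitivity table and one model term, with no extra patients or procedures. The price is a less favourable power statement for the enrolled population.

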#### Statistical analysis

Categorical variables will be presented as counts with percentages, e.g., *n* (%). Normally distributed data will be shown as the means with standard deviations, e.g., means ± SDs, while nonnormally distributed data will be expressed as medians with interquartile ranges, e.g., medians (IQRs). Student’s *t* test for continuous variables with normal distributions and the nonparametric

Kruskal–Wallis test for nonnormally distributed data will be applied for comparisons of significant differences between the 2 groups. The Pearson chi-square test will be used for categorical data. For binary observational endpoints, risk ratios with 95% confidence intervals will be calculated by binomial regression with and without adjustment for potentially confounding baseline values. In this study, the main analyses will be conducted using an intention-to-treat (ITT) model, in which all participants will be included based on random assignment regardless of study completion. For outcomes collected at different time points, a repeated measurements design using a generalized estimating equation (GEE) model will be used to fit outcomes that are measured at each time point so that all the participants might be included in the analyses, even if there are missing data for some of the follow-up points. A multiple imputation model will be used to process the missing data. Additionally, statistical analyses of the baseline characteristics of participants who remain in the study and those who are lost to follow-up will also be performed to explore whether there is differential dropout. All statistical analyses will be conducted using the SPSS software (version 25.0) and R software (version 4.0.2). A two-sided *p* value < 0.05 will be considered significant.

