### Sample collection

Two vaginal swabs, 2 cervical canal swabs, and 3 ml of peripheral blood will be collected on the day of the first clinic visit and the day of embryo transfer (ET). Vaginal swabs will be collected directly, while cervical canal swabs will be collected carefully through a vaginal dilator device to avoid contamination from contact with the vagina. Vaginal and cervical canal swabs will be immediately collected in a clean 2-ml DNA LoBind tube and immediately placed on ice and transferred to a − 80 °C freezer within 2 h, followed by DNA extraction. Peripheral venous blood will be collected in coagulation-enhancing disposable vacuum blood collection tubes. Blood will be centrifuged at 2000 rpm for 20 min at 4 °C (Eppendorf, Germany). Serum will be isolated and divided into 2 tubes and immediately frozen at − 80 °C until use.

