### Participant timeline

The time schedule of enrollment, intervention, follow-up and outcome assessments is shown in Table 3. After undergoing ovulation, egg retrieval, IVF, and advanced embryo freezing, PCOS patients will move on to the next step of endometrial preparation for FET. The duration of endometrial preparation will continue for approximately 14 days. At the 1st clinical visit on the first day of the current FET cycle, written informed consent, baseline information, 2 vaginal swabs, 2 cervical canal swabs, and 3 ml peripheral blood will be obtained at enrollment. After quick screening for the relative abundance of *Lactobacillus* spp. in vaginal flora, the participants will be informed of whether they have LGT dysbiosis and the results of randomization. At the 2nd visit after enrollment, in the control group, participants with LGT dysbiosis will confirm the next contact, while the intervention group will administer live *Lactobacillus* capsules vaginally and will be provided a medication diary. All participants will be followed up 5 times in the clinic or by phone call. The 3rd visit after 5 days of drug administration will mainly be about whether any adverse response occurs. At the 4th visit after 10 days of drug administration, the medication diary will be checked and reviewed, and any adverse response will be recorded and reported. At the 5th visit on the day of ET, 2 vaginal swabs, 2 cervical canal swabs, and 3 ml peripheral blood will be obtained from participants in both groups. At the 1st follow-up after 14 days of ET, human chorionic gonadotropin (HCG) and progesterone (P) levels will be determined as standard clinical procedures. If the HCG test is positive, the 2nd follow-up will occur approximately 5 weeks after ET, and clinical pregnancy will be confirmed by ultrasound and recorded in the CRIP system. At the 3rd follow-up, the fetal developmental situation and maternal obstetric complications at approximately 24-28 gestational weeks, if any, will be carefully recorded. The endpoint of follow-up is live birth, and maternal and neonatal information will be obtained.

**Table 3 Tab3:** Schedule

	1st visit on FET initial day	2nd visit after enrollment	3rd visit after 5 days	4th visit after 10 days	5th visit on ET	1st follow-up at 14 days after ET	2nd follow-up at 5 weeks after ET	3rd follow-up at mid-pregnancy	End of live birth

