**Assessments**									
Baseline questionnaire	**X**								
Vaginal and cervical canal swabs	**X**				**X**				
Peripheral blood samples	**X**				**X**				
Medication diary (intervention group)		**X**	**X**	**X**					
HCG and P						**X**	**X**		
Clinical pregnancy							**X**		
Maternal and Fetal information							**X**	**X**	**X**
Safety assessment		**X**	**X**	**X**	**X**	**X**	**X**	**X**	**X**

*HCG*, human chorionic gonadotropin; *P*, progesterone

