### Microbiome and metabolism

Alpha and beta diversity analysis will be conducted by QIIME2 software [23]. The taxonomy abundance spectrum will be described and compared between groups using the linear discriminant analysis effect size (LEfSe) method. Metabolic profiles will be analyzed using the Progenesis QI v3.0 software.

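### Swab and blood measures have one pre-treatment and one ET-day value: the GEE sentence, read literally, makes the first-visit value a response, and the plan should state that it is used for baseline adjustment

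*Protocol article*

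**What the plan says.** The Statistical analysis section of the protocol article assigns outcomes collected at more than one time to a GEE: "a repeated measurements design using a generalized estimating equation (GEE) model will be used to fit outcomes that are measured at each time point". The reason given is that all participants might then be analysed, "even if there are missing data for some of the follow-up points". The section does not state the model terms, the working correlation or the role of the first-visit value. For continuous data it otherwise offers a t test or a Kruskal–Wallis test. Adjustment for baseline values appears only with the binomial regression for binary endpoints. Multiple imputation is planned for missing data.

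Swabs and blood are taken twice in both arms. The first set comes at the first clinic visit, before any capsule is used. For the second, Participant timeline says: "At the 5th visit on the day of ET, 2 vaginal swabs, 2 cervical canal swabs, and 3 ml peripheral blood will be obtained". In Table 3 the swab row and the row "Peripheral blood samples" are marked at these two visits only. The abstract gives the purpose of the laboratory work: to "evaluate the LGT microbiome and systemic metabonomics before and after the intervention".

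The section Microbiome and metabolism names QIIME2 for diversity and Progenesis QI for metabolic profiles. For taxa it says: "The taxonomy abundance spectrum will be described and compared between groups using the linear discriminant analysis effect size (LEfSe) method". It does not say how the first-visit sample enters a comparison of the arms.

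**The concern.** A GEE over several time points suits an outcome with several post-treatment values. Here there is one, and the other value precedes treatment, so the arms can differ on it only by chance. A model that fits both values as responses gives the intended contrast only if its terms are chosen with care. One common choice averages the treatment effect with a baseline difference of zero. Another subtracts the whole baseline value and adds noise. The remaining stated rules for continuous data ignore the first-visit value altogether.

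At stake is the estimated effect on the vaginal and cervical flora and on serum metabolites. Reversing dysbiosis is the first aim named under Objectives, so an understated or needlessly imprecise result would matter, although these measures are not listed among the primary or secondary outcomes.

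**Working it through.** **Plan's own figure.** The plan states no figure for the GEE or for any swab or blood measure. Its only sample-size figure concerns clinical pregnancy. At 17.65% versus 37.65%, one-sided alpha 0.025 and 95% power, I obtain 127 per group (254 in total). The planned 130 per group gives 95.4% power. Nothing below touches that calculation.

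**Inputs.** From the documents: two samples per woman (first visit and ET day), 1:1 allocation, 130 per group in the sample-size statement. Assumed, because the documents are silent: pre-post correlation r of 0.3, 0.5 or 0.7, equal variances (set to 1) at both times, complete data. Let d be the arm difference on ET day and n the number per arm.

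**Formulas.**
- Baseline-adjusted regression: estimates d, variance (1 − r²)·2/n.
- GEE with arm and time only: the arm coefficient is (0 + d)/2 = d/2, variance [(1 + r)/2]·2/n.
- GEE with unconstrained arm-by-time: difference in mean change, estimates d, variance 2(1 − r)·2/n. Ratio to baseline adjustment: 2(1 − r)/(1 − r²) = 2/(1 + r).
- ET-day values compared without adjustment: estimates d, variance 2/n. Ratio: 1/(1 − r²).

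**Results.** The power columns take the d at which baseline adjustment has 80% power with 130 per arm, two-sided 0.05.

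| r | Variance ratio, arm-by-time | Variance ratio, ET-day only | Power, arm-by-time | Power, ET-day only | Power, arm + time |
|---|---|---|---|---|---|
| 0.3 | 1.54 | 1.10 | 62% | 76% | 38% |
| 0.5 | 1.33 | 1.33 | 68% | 68% | 29% |
| 0.7 | 1.18 | 1.96 | 73% | 52% | 19% |

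**Simulation check** (130 per arm, true d = 0.40 SD, exchangeable GEE, 300 runs per r).
- Arm + time: mean estimates 0.204, 0.189 and 0.190 at r = 0.3, 0.5 and 0.7, about half of 0.40.
- Unconstrained arm-by-time: mean 0.39 to 0.40, variance ratios 1.49, 1.29 and 1.13, close to the formula.
- GEE with a common baseline mean (time and arm-by-time terms, no arm main effect): mean 0.39 to 0.40, variance ratio 1.00 at each r. This form loses nothing.

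**If the variances differ.** Let k be the baseline SD divided by the ET-day SD. The arm-by-time ratio becomes (1 + k² − 2rk)/(1 − r²) = 1 + (k − r)²/(1 − r²). At k = 1 this is 2/(1 + r), and it is never below 1. The entry limit of under 80% Lactobacillus may narrow the baseline spread. For example, k = 0.7 with r = 0.5 gives 1 + 0.04/0.75 = 1.05, a much smaller loss for that measure.

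**The case against.** A reader might infer that the plan commits itself to a halved effect. The documents do not support that. Halving needs a model with arm and time terms only, and no terms are stated. The reference to follow-up points can be read as post-baseline points, with the first-visit value as a covariate. A GEE that uses both samples as responses under a common baseline mean is also compatible with the text and fully efficient. The arm-by-time form is unbiased, so its cost is precision only.

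A reader might also infer that the GEE sentence is aimed at the swab and blood data. It does not name them, and Microbiome and metabolism gives LEfSe and software for some of these measures. Table 3 offers other repeated items: safety assessment at eight points, maternal and fetal information at three, HCG and progesterone at two. These are reasons to keep the sentence. Most fit it poorly, however. The second HCG and progesterone value depends on the first result ("If the HCG test is positive, the 2nd follow-up will occur approximately 5 weeks after ET"), and the maternal and fetal entries record different events at each visit.

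Model terms are often left to a statistical analysis plan, which is not shown, so their absence is not a fault in itself. Nor is it a strong complaint that GEE relies on data missing completely at random, because multiple imputation is planned.

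What survives is narrower. The literal wording makes the first-visit value a response, and no stated rule for continuous measures adjusts for it. If follow-up points means post-baseline points only, one value per woman remains and there is nothing repeated to model.

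**Conclusion.** The point holds as a worthwhile, low-cost correction. For continuous measures with one first-visit and one ET-day value, the GEE sentence read literally allows analyses that either report about half the ET-day effect (arm and time terms only) or carry 1.18 to 1.54 times the variance of a baseline-adjusted analysis (unconstrained arm-by-time, r from 0.7 to 0.3). In that second case it is as if 18% to 54% more women were needed for the same precision. An unadjusted ET-day comparison costs a factor of 1.10 to 1.96 over r from 0.3 to 0.7.

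These figures rest on assumed correlations and complete data. The arm-by-time ratios also need equal variances, and would be smaller where the entry criterion compresses the baseline. The plan does not fix the form of the GEE, so these are consequences of permitted forms and not of a declared model. Only the microbiome and metabolite measures are affected. Clinical pregnancy is assessed once and has its own binomial regression, so the primary analysis and the sample size stand.

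**What to change.** Keep the GEE sentence for other repeated outcomes and add one rule to Statistical analysis:

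- For each continuous measure with a first-visit and an ET-day sample, the arm effect is the ET-day difference between arms with its 95% CI.
- It is estimated by regressing the ET-day value (transformed if skewed) on arm, with the first-visit value as covariate. A GEE that constrains the arms to a common baseline mean is an acceptable equivalent; the simulation confirmed the equivalence under equal variances.
- Missing ET-day values are handled by the multiple imputation already planned, with arm and the first-visit value in the imputation model.

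The cost is one added rule in the text. It needs no new samples, visits or participants, because both samples are already scheduled in both arms.

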## Methods/design

### Objectives

We plan to conduct the present trial to evaluate the effects of supplementation with live *Lactobacillus* capsules for vaginal use on reversing LGT dysbiosis and improving perinatal outcomes in PCOS patients undergoing IVF-FET.

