### Liquid chromatography–mass spectrometry (LC–MS) for metabonomic analysis

An ACQUITY UPLC I-Class system (Waters Corporation, Milford, USA) coupled with a VION IMS QTOF mass spectrometer (Waters Corporation, Milford, USA) will be used to analyze the metabolic profile in both ESI positive and ESI negative ion modes.

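### The only significance rule is a blanket two-sided p < 0.05, and the only named taxon-level comparison is LEfSe, so false discoveries among taxa are not controlled

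*Protocol article*

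**What the plan says.** Three parts of the protocol article bear on this point.

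- **Threshold.** The Statistical analysis section ends with a software statement, "All statistical analyses will be conducted using the SPSS software (version 25.0) and R software (version 4.0.2", followed at once by "A two-sided *p* value < 0.05 will be considered significant". No other significance rule appears in the article. No multiplicity or false discovery procedure is named for any analysis.
- **Taxa and metabolites.** The Microbiome and metabolism section says "The taxonomy abundance spectrum will be described and compared between groups using the linear discriminant analysis effect size (LEfSe) method". It also plans community-level measures ("Alpha and beta diversity analysis will be conducted by QIIME2 software [23") and, for metabolites, names only software: "Metabolic profiles will be analyzed using the Progenesis QI v3.0 software". The LC–MS section adds that the instrument "will be used to analyze the metabolic profile in both ESI positive and ESI negative ion modes". Neither section gives a p threshold, an LDA cutoff, a number of features or a decision rule.
- **Objective.** The Objectives section says the trial evaluates the capsule's effect "on reversing LGT dysbiosis and improving perinatal outcomes in PCOS patients undergoing IVF-FET". The primary and secondary outcome sections list no microbiome or metabolite endpoint.

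The Sample collection section provides for vaginal and cervical canal swabs and blood at the first visit and on the day of embryo transfer.

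**The concern.** LEfSe screens each taxon with its own rank test and then ranks the survivors by an LDA effect-size score. Neither step limits the number of false discoveries over the whole profile. The screen is of the same kind as the Kruskal–Wallis test that the Statistical analysis section prescribes for non-normal data, so the general 0.05 threshold is the natural one to carry over.

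Applied that way to many taxa, the rule yields a list of differing taxa partly, or under no effect wholly, made of chance findings. Restoring the lower genital tract flora is a stated aim beside pregnancy, and no single flora endpoint is listed as its test. A reader of the results would therefore be likely to lean on that list, both for the flora objective and to explain the pregnancy result.

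**Working it through.** **Inputs**

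- Threshold per test: 0.05, two-sided (Statistical analysis section).
- Number of taxa tested, m: not given. Assumed 50, 100 and 200 per site.
- Correlation between taxa: not given. Taken as 0 (independent), 0.3, 0.5 and 0.8.
- LDA cutoff: not given. The figures below apply before any cutoff.
- Each test is assumed to hold its nominal 5% level.

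The article states no error rate for the microbiome or metabolite analyses, so there is no figure of its own to reproduce. Its sample size concerns clinical pregnancy and does not enter here.

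**Step 1. Expected number of false taxa when none has changed: 0.05 × m**

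- m = 50: 0.05 × 50 = 2.5
- m = 100: 0.05 × 100 = 5
- m = 200: 0.05 × 200 = 10

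This expectation does not depend on correlation. If both sites are sequenced and tested, it doubles to between 5 and 20.

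**Step 2. Chance of at least one false taxon, independent tests: 1 − 0.95^m**

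- m = 50: 92.3%
- m = 100: 99.4%
- m = 200: more than 99.9%

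The chance first reaches 95% at m = 59 (95.2%).

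**Step 3. The same chance with correlated tests**

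Simulation of equally correlated null z-statistics, 20,000 replicates:

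| m | correlation 0.3 | correlation 0.5 | correlation 0.8 |
|---|---|---|---|
| 50 | 80.4% | 62.6% | 30.0% |
| 100 | 94.4% | 78.3% | 36.1% |
| 500 | 100% | 99.0% | 50.9% |

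Correlation lowers the chance of any false hit. Because the expected number is unchanged, the hits then come in larger clusters.

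**Step 4. With Benjamini-Hochberg at 5%**

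In the same simulation, with m = 20, 50, 100 and 500 and correlations from 0 to 0.8, the chance of any declared difference under no effect was 1.5% to 5.4%. With independent tests it was about 5% for every m.

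**Step 5. Metabolites, conditionally**

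No test is stated. If 1,000 signals (an assumed count) were each read at 0.05, 0.05 × 1,000 = 50 would be expected to pass by chance in one comparison.

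**The case against.** The strongest reply is that the criticised rule is assembled rather than written. The article never says that taxa are judged one by one without adjustment. The threshold closes a section on clinical methods, while the microbiome work has its own section and its own tools. False discovery handling and LDA cutoffs are often left to a full protocol or analysis plan, and neither is shown. This stands in part: the reading combines two sections, and an unseen plan may already adjust. It does not remove the point. The article states an unrestricted threshold next to a sentence covering all statistical analyses, and it fixes a whole-profile comparison method that does not control false discoveries. If adjustment is planned elsewhere, the stated rule still needs that exception.

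A second reply is that LEfSe also filters on effect size. That is true, and a cutoff could reduce the counts in Step 1. By how much depends on a value the article does not give, and the filter is not an error-rate control.

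A reader might also infer that a finding that treatment changed the flora is almost certain even if the capsule does nothing. The documents do not support that. No section turns one differing taxon into a claim of reversed dysbiosis. Eligibility is defined by *Lactobacillus* share, specific *Lactobacillus* species and *Gardnerella vaginalis* are named qPCR targets, and alpha and beta diversity are planned. A random unrelated taxon would not show reversal. Serum metabolites are not flora, and no metabolite test is stated at all. Near-certainty of even one false taxon needs many tests and weak correlation, and neither is documented.

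**Conclusion.** The point holds in a limited form. Following the two sections as written, about 5% of unchanged taxa would be expected to pass the p-value screen: about 2.5 to 10 per site for an assumed 50 to 200 taxa, before any LDA cutoff. The chance of at least one runs from 92% to more than 99.9% under independence, but for 100 taxa it falls to about 78% at correlation 0.5 and 36% at 0.8. The taxon counts and correlations are assumptions, and applying the 0.05 threshold to taxa is an inference, though the plain one.

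What is affected is the credibility of individual taxon findings and any statement about the dysbiosis objective built on them. The metabolite part is conditional on the same threshold being used. The clinical pregnancy conclusion is untouched.

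**What to change.** Add to the analysis section:

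- The p < 0.05 rule does not govern feature-level scans.
- Taxon-level between-arm differences, and metabolite-level ones if tested, are declared only at a Benjamini-Hochberg false discovery rate of 5% within each site and ion mode, using a between-arm test that gives a p value per feature.
- LEfSe scores are reported as a descriptive ranking, and no conclusion on reversal of dysbiosis is drawn from unadjusted LEfSe hits.

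If an existing analysis plan already does this, a cross-reference to it as an exception to the general threshold is enough. The change should be dated before these data are analysed by arm.

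The cost is a few sentences and a routine adjustment in R, which the article already names. Nothing changes for participants. The downside is fewer flagged taxa and metabolites, including some real differences that would have passed an unadjusted screen.
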